### Environmental data collection

Environmental assessment will include thermal drone surveys to evaluate heat accumulation and dissipation across structures. Surveys will be conducted at baseline and annually at three time points: sunrise (within 2 hours), mid-day (12:00–16:00) and sunset (1 hour before and after sunset).

Indoor temperatures will be recorded in all households using thermochron ibuttons at 20-minute intervals. Outdoor temperature and humidity will be measured using HOBO weather stations and Kestrel Drop 2 devices (also at 20-minute intervals). These devices have been validated globally and serve as standard environmental monitoring tools. In addition, local weather station data will be used to obtain daily measures of ambient temperature, relative humidity, wind speed and solar radiation throughout the study period. Heat stress indices will be derived from these parameters, including the Universal Thermal Climate Index (UTCI) and Wet Bulb Globe Temperature.

Designated staff will routinely retrieve data from installed and wearable devices and return them after transfer. In areas with limited internet connectivity, data will be manually exported onto secure USB devices and stored on password-protected laptops. All data will be archived in a secure repository at Aga Khan University (AKU), Karachi, with access restricted to authorised personnel via institutional network credentials. Role-based permissions will ensure confidentiality. The repository will be synchronised daily with a secure remote backup to prevent data loss or corruption.

### Devices

The devices and their utilisation for outcome measurements are provided in table 2.

**Table 2 T2:** Devices used for outcome measures

Outcome measures	Device	Placement
Individual and household level exposure	Thermochron ibuttons, Temp-U which record temperature and humidity	Put at select households in the intervention and control clusters within the main living room, midway between floor and ceiling and away from any direct heat source. Devices will be given to individuals selected for subgroup for individual exposure assessment
Environmental exposure	Kestrel 5400 which will record multiple environmental parameters like wet bulb globe temperature, solar radiation, barometric pressure, wind speed and humidity	One device rotated in each cluster
Individual physiological outcomes	Fitbit Inspire 3 wearable fitness tracker that will track heart rate, sleep cycles, activity levels and energy consumption	Given to the subset population selected in the intervention and control clusters
Weather	Kestrel drop D2 and HOBO U-30 weather stations	One weather station placed at the field office as a central location and one Kestrel drop D2 placed in each cluster

### Data collection from subset population

Monthly data will be collected from the subset population to provide detailed insights into heat stress and intervention effectiveness (table 3). This will include assessment of thermal comfort, mental health and heat exposure.

**Table 3 T3:** Schedule of outcome assessments and follow-up activities

Parameter	Time points	Details	Devices/tools	Population/unit
Primary outcomes				
All heat-related illness	Weekly during peak summers	Heat-related illnesses	Weekly community survey, health facility data, community surveillance	All members of included households
Quality of life	Mid of April, July and December for two consecutive years	Quality of life mean score	WHOQOL-BREF* questionnaire	Indexed adults of all included households
Secondary outcomes				
All-cause mortality	Weekly during peak summers	Any mortality occurring within the included clusters	Weekly community survey, health facility data, community surveillance	All members of included households
Hospital visit/hospitalisation	Weekly during peak summers	Any hospital admission or hospital visit occurring within the included clusters	Weekly community survey, health facility data, community surveillance	All members of included households
Indoor Heat Index	Continuous throughout the year	Indoor data loggers	Ibutton, Kestrel Drop D2, Temp-U	All included households
Thermal comfort (home)	Monthly	Self-reported comfort levels	Thermal comfort survey adapted from CHEQ-5‡	Indexed adults randomised for subgroup
UTCI	Continuous throughout summers	Outdoor only	Kestrel Drop D2, Kestrel 5400, HOBO weather station	Overall catchment area
Outcomes measured for subset of population				
Personalised heat exposure	Baseline, Monthly	Occupation, sun exposure, illness history, daily routine	Structured survey tool (adapted from HotHaps) and Temp-U	Indexed adults randomised for subgroup
Physiological strain markers	Continuous throughout summers	Heart rate, sleep cycles, VO₂ max†	Fitbit Inspire 3	Indexed adults randomised for subgroup

Participant compliance will be monitored through spot checks and periodic review of device data. For Fitbit devices, heart rate data will be reviewed, as prolonged absence of heart rate recordings may indicate that the device was not worn. Similarly, iButton and Temp-U data will be checked periodically for implausible temperature spikes or sudden drops, which may indicate non-compliance or incorrect device use.

* WHO Quality of Life Brief tool.

† Maximum Volume of Oxygen.

‡ Cold and Heat Evaluation Questionnaire.

UTCI, Universal Thermal Climate Index.

Individual heat exposure will be measured among a subset of participants (eight per cluster) using thermochron ibuttons or TempU devices attached to clothing. Participants will be instructed to always wear the device and to place it beside their bed while sleeping.

Participants in the subset will also be provided with Fitbit Inspire 3 devices to capture physiological parameters, including heart rate, body temperature variation, sleep, energy expenditure and physical activity. These devices will be synchronised weekly with the AKU server, charged and returned to participants.

### Statistical analysis

The trial has two co-primary outcomes, heat-related illness and quality of life. These outcomes will be evaluated independently to assess the effectiveness of the intervention. All statistical analyses will be conducted using STATA V.18.0 (https://www.stata.com), following an intention-to-treat approach while accounting for the cluster-randomised trial design. Baseline characteristics will be analysed to assess comparability between intervention and control arms. Descriptive statistics will summarise household and participant characteristics, and any important imbalances at baseline will be adjusted for in the analysis. No interim analysis or formal stopping guidelines are planned given the low-risk nature of the intervention.

Statistical analyses will account for the cluster-randomised design by incorporating clustering through random effects or robust variance estimators, as appropriate. For outcomes measured repeatedly over time, within-participant correlation will be accommodated using repeated-measures mixed-effects models. Intervention assignment and seasonal variation will be included as fixed effects in all applicable models, while relevant baseline covariates and baseline outcome values (where available) will be adjusted for. Model assumptions, including overdispersion for count outcomes, will be assessed and alternative modelling approaches (eg, negative binomial models) will be used where appropriate. Missing data will be examined and handled using complete-case analyses or multiple imputations, depending on the extent and pattern of missingness. Sensitivity analyses will be performed to assess the robustness of findings to different assumptions regarding missing data.

#### Primary outcome analysis

For each participant, a summary record will be constructed comprising the number of heat-related illness episodes and the number of assessment occasions (or person-time) over which the individual was observed. To assess the intervention effect, a Poisson regression model with cluster-level random intercepts will be used, accounting for intracluster correlation. The number of heat-related illness episodes/events will serve as the numerator, while person-weeks at risk will be used as the denominator. Results will be presented as incidence rate ratios (IRRs) with 95% CIs.

Duplicate reports identified across multiple sources will be flagged in the database using participant ID, household ID, date of onset, symptoms and care-seeking information to ensure that each event is counted only once. Symptoms or events continuing from a previous reporting period will be considered part of the same illness episode. A new episode will be defined as either the onset of symptoms following a symptom-free interval of at least 2 days after the previous episode or the occurrence of additional new symptoms in a participant with ongoing previously reported symptoms. For quality-of-life assessments, changes from year one to year two will be compared across three assessment points per year. Summer and winter quality-of-life scores will also be analysed separately. Results will be reported as adjusted mean differences with 95% CIs.

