### Study design

This study is a 2-year prospective, cluster-randomised controlled trial designed to evaluate the effectiveness of ReHAB intervention in rural settings. One village will serve as one cluster with 70–80 households randomized, and these clusters will be randomly assigned to either the intervention or control arm in a 1:1 ratio (figure 1). Due to the nature of the intervention, blinding of participants and researchers will not be feasible, but data analysis would be blinded. The trial is registered on clinicaltrial.gov with trial registration number NCT06983483. The study field activities will run from 1 January 2026 to 31 December 2027.

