### Sample size

Sample sizes were calculated for both the primary outcomes to provide at least 80% power at the 5% significance level. Based on heat-related symptoms and illness prevalence of 28.9%^21^ and an estimated intracluster correlation coefficient (ICC) of 0.0122, we calculate that 11 clusters per arm (22 clusters in total) with 70 to 80 households per cluster are needed to detect a 30% relative difference in heat-related illnesses while allowing for a 10% attrition rate. We treat 28.9% as a conservative estimate given the longitudinal nature of the primary outcome, as cumulative prevalence over the surveillance period is expected to exceed this single-time point prevalence. To assess quality of life changes, we estimate that with 11 clusters per arm 60 households per cluster are required based on the variability in baseline WHO Quality of Life Brief tool (WHOQOL-BREF) scores reported in Lodhi *et al*,^22^ which documented an average score of 68 (18.0) to detect a difference of 4 points in quality of life score assuming an ICC of 0.015. As the heat-related illness outcome required the larger sample size, the final enrolment target was set at 70–80 households per cluster, which also provides adequate power for the quality-of-life outcome. To assess physiological heat strain, we calculated that a subsample of eight adults (aged 18 years to 60 years) per cluster (balanced by gender) would be required to detect a 15% change in average heart rate, among those who are exposed to heat stress assuming a baseline of 66±12 bpm,^23^ an ICC of 0.1736 and 90% power. Given the complexity of the assessment process, we anticipate a higher attrition rate in this subset and have inflated the sample size by 30% to 10 individuals.

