##### Community education and awareness

The educational component of ReHAB was developed based on findings from the formative phase, including systematic review, qualitative work, stakeholder consultations and pilot testing. Community mobilisation will be implemented throughout the intervention. Community groups (CGs) will be established across all 11 intervention clusters, with separate male and female representation. Each CG (6–8 members) will include local government representatives, elders, religious leaders and male and female community members. CGs will lead mobilisation activities and support surveillance of the primary outcome (heat illness).

Activities will include dissemination of heatwave warnings, awareness sessions and door-to-door outreach on heat-health practices (hydration, clothing and activity scheduling). CGs will maintain logbooks to record healthcare visits within their catchment areas and attendance in community meetings. Practical demonstrations of cooling strategies (eg, shade setup, light clothing, wet towels, misting and work–rest–shade cycles) will be conducted, supported by Information, Education and Communication (IEC) materials. This structured, behaviour-focused delivery aims to ensure both the uptake and sustainability of protective cooling practices. Community hydration measures (eg, temporary drinking water facilities) will also be implemented to reduce dehydration among outdoor workers.

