Data on signs and symptoms of heat-related illness will be collected through multiple sources to minimise missed events during the study period in the intervention and control clusters. Suspected heat-related illness episodes identified through community surveillance, household surveys or health facility records will be classified according to the predefined symptom-based algorithm by study data collectors as presented in figure 2 and categorised using International Classification of Disease, 11th Revision and institutional criteria. Events that would be identified through community surveillance will be visited by data collectors who will use the same survey tool, and reported health facility visits will be verified through facility records, where feasible. Quality of life data will be obtained through repeated household surveys, with the selected index adult serving as the respondent (Table 3).

Quantitative data will be collected using handheld devices with a custom-built Java application, with MySQL and SQLite used for data storage. Built-in range checks, consistency checks and skip patterns will minimise data entry errors. Any discrepancies will be verified and resolved through follow-up with data collectors. Each participant will be assigned a unique identifier generated by the purpose-built Android application to maintain anonymity. All data will be securely stored behind firewalls and fully anonymised prior to analysis.

In the second year of intervention, 5 mL venous blood samples will be collected from participants in both intervention and control households during peak heat time. Samples will be obtained by trained phlebotomists using standard aseptic techniques and stored in a biobank according to established protocols. These samples may be used for future exploratory analysis of heat-related biomarkers which have not been specified yet.

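### The quality-of-life co-primary is written as a change from year one to year two, but year one is also an intervention year, so the contrast measures growth in the effect and not the 4-point difference that was powered

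*Protocol article*

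**What the plan says.** The only sentence in the protocol article that sets the comparison for QoL is in Primary outcome analysis: "changes from year one to year two will be compared across three assessment points per year". It adds that summer and winter scores will also be analysed separately, and that results will be reported as adjusted mean differences.

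On timing, Study design states: "The study field activities will run from 1 January 2026 to 31 December 2027". Table 3 schedules QoL at "Mid of April, July and December for two consecutive years", which makes six visits. Household data collection places blood sampling in a later year of treatment: "In the second year of intervention, 5 mL venous blood samples will be collected". Community education and awareness says "Community mobilisation will be implemented throughout the intervention", and the Sessions list covers every month of the year, with fortnightly meetings from April to June.

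On the quantity of interest, Sample size plans 11 clusters per arm and 60 households per cluster "to detect a difference of 4 points in quality of life score assuming an ICC of 0.015". The same section says that each co-primary is powered at 80% or above, and that the repeated-measures mixed model gains precision by combining visits. Statistical analysis adds: "Intervention assignment and seasonal variation will be included as fixed effects in all applicable models", with adjustment for baseline outcome values where available.

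**The concern.** If year one were a pre-intervention year, a change from year one to year two would be an ordinary change from baseline. The protocol does not describe year one that way: a second year of intervention implies a first. At least July and December of year one then fall in the intervention period, and subtracting year one from year two removes whatever benefit was already present.

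QoL is a co-primary outcome and the second step of the fixed-sequence test. An intervention that works from the first summer and keeps working could yield a confirmatory QoL estimate near zero. One that works well at first and then weakens could yield an estimate in the direction of harm. The protocol also carries two incompatible descriptions of the same co-primary analysis, which leaves room to choose between them after the data are seen.

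**Working it through.** **1. The plan's own figure.** Inputs from Sample size: difference 4, SD 18.0, ICC 0.015, 80% power, alpha 0.05 (taken as two-sided), k = 11 clusters per arm.

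- Individuals per arm without clustering: n = 2 × [18 × (1.960 + 0.842) / 4]² = 317.9.
- Cluster size: m = n(1 − ICC) / (k − n × ICC). With k = 11, m = 313.1 / 6.23 = 50.2. With the usual small-sample allowance of one cluster per arm (k = 10), m = 313.1 / 5.23 = 59.8, that is 60.
- Check at m = 60, k = 11: SE = 18 × √(2 × (1 + 59 × 0.015) / 660) = 1.36. Power is 79.9% (t, 20 df) or 83.7% (normal).

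The stated 60 per cluster is reproduced. It is the sample size for a difference in *score* between arms at one time point.

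**2. Expected value of the contrast as written.** Let d₁ to d₆ be the true arm differences at April, July and December of year one, then of year two. The change contrast is (d₄ + d₅ + d₆)/3 − (d₁ + d₂ + d₃)/3. This step needs no variance assumption.

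| True arm differences (year one; year two) | Expected contrast |
|---|---|
| 4, 4, 4; 4, 4, 4 | 0 |
| 0, 4, 4; 4, 4, 4 (only April of year one untreated) | 4 − 8/3 = 1.33 |
| 3, 3, 3; 4, 4, 4 | 1 |
| 2, 2, 2; 4, 4, 4 | 2 |
| 4, 4, 4; 2, 2, 2 (fading) | −2 |
| 0, 0, 0; 4, 4, 4 | 4 |

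The full 4 points is recovered only if all three year-one visits precede the intervention, which conflicts with the reference to a second year of intervention.

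**3. Power of that contrast.** This needs correlations that the protocol does not give. Assumed: exchangeable within-person correlation ρ from 0.3 to 0.7, cluster autocorrelation 0.8, t with 20 df, 60 per cluster.

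- Variance components: between clusters 324 × 0.015 = 4.86; within clusters 324 × 0.985 = 319.14.
- The squared contrast weights sum to 6 × (1/3)² = 2/3 and the weights sum to 0, so each component is multiplied by (2/3)(1 − correlation).
- SE² = 2 × [4.86 × (2/3)(0.2)/11 + 319.14 × (2/3)(1 − ρ)/660]. SE = 0.75 at ρ = 0.3 and 0.56 at ρ = 0.7.

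| Expected contrast | Probability of rejection |
|---|---|
| 0 | 5% |
| 1 | 24–40% |
| 1.33 | 39–62% |
| 2 | 71–93% |
| −2 | 71–93%, in the direction of harm |

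**4. The pooled alternative.** Under the same assumptions, a constant 4-point benefit averaged over all six visits has expected value 4.0, SE 1.07 to 1.21 and power of about 88–95%. Averaged over the five visits after April of year one, each component is multiplied by (1/5)(1 − correlation) + correlation. SE is then 1.08 to 1.22 and power about 88–94%. Both SEs are below the planning value of 1.36.

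**The case against.** The strongest reply is that one loose sentence is being read too hard. It does not mention arms, does not define a difference of yearly averages and is not labelled as the hypothesis test. Much of the document points to a level difference: Table 3 lists the outcome as a mean score, Table 1 defines no change score, Sample size powers a difference in score, and Statistical analysis enters arm as a fixed effect. On that view the right model is already planned.

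What stands of this is that the intended analysis may well be sound. But general statements do not override the one outcome-specific sentence. If the general model is what is meant, that sentence misdescribes it and still has to change.

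Four stronger readings are tempting, and the documents do not support them:

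- *The benefit always cancels completely.* This holds only for an effect that is equal in both years. The text shown does not date the completion of the structural work, so the effect may build up and cancellation may be partial.
- *Power falls to 17% for 1.33 points and 31% for 2 points.* A reader who puts the planning SE of 1.36 into the change contrast gets these figures. That SE is for a single visit, whereas the contrast averages three visits per year and has a smaller SE.
- *The protocol holds three different QoL quantities.* It holds two. For a constant effect, the pooled mixed-model difference is the same 4-point difference used in the sample size, estimated more precisely.
- *A sustained benefit would go unseen.* The separate summer and winter analyses could show it. They are additional, however, and do not replace the co-primary comparison.

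**Conclusion.** The sentence is wrong as written and should be corrected before analysis. Read as a between-arm comparison, it estimates the growth of the effect from year one to year two. That contradicts both the difference in score that was powered and the mixed model described in Sample size and Statistical analysis.

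That the contrast is zero for a constant 4-point benefit, with a 5% rejection rate, rests only on all six visits being on intervention. The 1.33-point value assumes that April of year one alone is untreated, and no section says whether it is. Power in the partial cases depends on the assumed correlations and should be quoted as ranges. The claim of at least 80% power belongs to the level difference and cannot be carried over to the year-to-year change. The sample size figure of 60 per cluster is not in question.

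**What to change.** Replace the sentence in Primary outcome analysis. Define the QoL co-primary as the adjusted between-arm mean difference in WHOQOL-BREF score, averaged over the post-baseline visits. Estimate it from the repeated-measures mixed model already planned, with arm, visit or season, and baseline QoL.

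State which QoL visit is the pre-intervention baseline. April of year one can serve only if it precedes delivery in the intervention clusters; if it does not, average over all visits and do not use April as the baseline covariate. Keep the year-one-to-year-two change, compared between arms, as a secondary analysis of whether the effect builds up or fades.

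The cost is one paragraph of protocol and analysis-plan wording, settled before outcome data are examined by arm. No new data and no change in sample size are needed.

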### Outcomes

All primary, secondary and outcomes assessed for subset of population along with definitions are provided in table 1 and figure 2.

**Table 1 T1:** Outcomes

Primary outcomes	
Heat-related illness	Defined as a documented heat condition/illness according to the International Classification of Disease-11th Revision and institutional classification which classifies heat-related illness as heat stroke, heat syncope, heat exhaustion, heat fatigue, heat cramps and heat rash (figure 2).^30 31^
Quality of life	Quality of life would be assessed according to the WHOQOL-BREF* tool and assessed during two consecutive peak summer and winter seasons.

Secondary outcomes	
Health outcomes	
All-cause mortality	Defined as the total number of deaths in the study population over the study period
Hospital visit/hospitalisation	Defined as the number of hospital admissions (primary, secondary or tertiary facilities) during summers
Environmental outcomes	
Heat Index	Indoor heat index (temperature and humidity)^32^ measured through fixed weather devices
Universal Thermal Climate Index	Defined as a biometeorological index that describes the human body’s physiological response to the environment. It integrates air temperature, humidity, wind speed and radiant temperature to assess the overall thermal stress on the human body
Thermal comfort	Defined as change in the condition of mind that expresses satisfaction with the thermal environment
Outcomes measured for subset of population (individual level)	
Personalised heat exposure	Defined as mean daily external temperature each individual experiences (indoors and outdoors) as recorded by a wearable temperature monitor.
Heart rate	Defined as mean heart rate measurements (beats per minute) taken at 1-hour interval as recorded by wearable android device
Sleep quality	Defined as a biological process that alternates between non-rapid eye movement sleep and rapid eye movement sleep as recorded through a wearable android device
Physical activity	Defined as mean daily duration of sedentary, lightly active, moderately active and very active as measured using a wearable android device.
Energy expenditure	Defined as average total number of calories burned in a day recorded using a wearable android device.
Economic outcomes	
Cost-effectiveness	Measured as the difference in cost divided by the difference in health effect between the intervention and control groups

* WHO Quality of Life Brief tool.

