For binary outcomes, the ICC was derived from an assumed cluster-level prevalence variation of ±10%, with the coefficient of variation (CV) estimated from this range and the ICC subsequently calculated using the relationship ICC=k²×P/(1−P), where k is the assumed between-cluster CV of the prevalence, following Pagel *et al*.^24^ For continuous outcomes, the ICC was estimated as the ratio of between-cluster variance to total variance,^25^ with total variance sourced from reference studies and a minimum between-cluster difference of ±9 units assumed. Each co-primary outcome is independently powered at 80% or above. To control the family-wise type I error rate across the two co-primary outcomes, hypotheses will be tested using a prespecified fixed-sequence (hierarchical) procedure: heat-related illness will be tested first at the two-sided 0.05 level, and quality of life will be tested at 0.05 only if the first test is significant. As each outcome is independently powered, this procedure incurs no loss of power. Quality of life is assessed at three time points per year over 2 years; the cross-sectional calculation above is therefore conservative, as the planned repeated-measures mixed-effects analysis increases precision by combining information across visits.

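### The quality-of-life test in step 2 of the fixed sequence is not tied to one contrast, so family-wise control is not secured when heat-related illness truly improves and quality of life does not

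*Protocol article*

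**What the plan says.** The Sample size section sets up a fixed sequence with this aim: "To control the family-wise type I error rate across the two co-primary outcomes". The illness outcome goes first, at two-sided 0.05. The rule for the second step reads: "quality of life will be tested at 0.05 only if the first test is significant". Step 2 is therefore one test.

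Four places describe what is done with quality of life:

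- **Sample size, power calculation:** a cross-sectional difference of 4 points between arms, with SD 18.0, ICC 0.015, 11 clusters per arm and 60 households per cluster.
- **Sample size, closing sentence:** a planned repeated-measures mixed-effects analysis that pools information over three visits per year for 2 years. The Statistical analysis section likewise plans repeated-measures mixed models, with intervention and season as fixed effects and adjustment for baseline values where available.
- **Primary outcome analysis:** "changes from year one to year two will be compared across three assessment points per year", followed by "Summer and winter quality-of-life scores will also be analysed separately". Results are reported as adjusted mean differences with 95% CIs.
- **Outcomes, Table 1:** quality of life is "assessed during two consecutive peak summer and winter seasons", whereas Table 3 schedules visits in mid-April, July and December.

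No sentence says which of these analyses is the step 2 hypothesis.

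**The concern.** A fixed sequence controls the family-wise error if each step is one prespecified hypothesis. Here the first step is named by outcome and has one model. The second is named by outcome only, and the protocol's own sections point to different contrasts for it. The gate protects against error between the two outcomes. It does not protect against a choice among contrasts inside the second.

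The contrasts also answer different questions. The bundle runs in both years; the Household data collection section speaks of a second year of intervention. A benefit that is the same in each year would show in the pooled difference and vanish from the year-on-year change. A benefit in July but not December would show in the summer analysis and not in the winter one. The verdict on a co-primary outcome could therefore turn on a choice made after the data are seen.

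**Working it through.** **1. What the protocol powers.** The inputs are in the Sample size section: difference 4, SD 18.0, ICC 0.015, 11 clusters per arm, m = 60, two-sided 0.05, 80% power.

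- Unclustered n per arm = 2 × (18/4)² × (1.960 + 0.842)² ≈ 318.
- Design effect = 1 + (60 − 1) × 0.015 = 1.885.
- Effective n per arm = 11 × 60 / 1.885 = 350.
- Power = 0.837 by normal approximation, or 0.799 by noncentral t with 20 df.

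The stated 60 households per cluster reproduces, and it does so for one between-arm difference at 0.05. It does not address a year-on-year change.

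**2. The two overall readings are different quantities.** Let d₁ and d₂ be the mean arm differences in years one and two.

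- Pooled reading: (d₁ + d₂)/2.
- Year-on-year reading: d₂ − d₁.

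If the benefit is the powered 4 points in both years, the pooled reading gives (4 + 4)/2 = 4 and the year-on-year reading gives 4 − 4 = 0.

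**3. False-positive chance if either overall reading may count.** Assume no true quality-of-life effect, an open gate, each contrast at two-sided 0.05, and equal variances and a common correlation among the six visit-level arm differences. The pooled and year-on-year contrasts are then uncorrelated whatever that correlation is. The chance is 1 − 0.95² = 0.0975, about 9.8%.

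**4. One overall contrast plus summer and winter.** The documents give no between-visit correlation, so 0.3, 0.5 and 0.7 are assumed. Simulation used 1,000,000 null draws of six visit-level differences, with July as summer, December as winter and |z| > 1.96 as positive:

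| Contrasts that could count | 0.3 | 0.5 | 0.7 |
|---|---|---|---|
| Pooled difference, summer, winter | 10.6% | 9.2% | 8.1% |
| Year-on-year change, summer, winter | 13.7% | 13.0% | 12.3% |

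The range is roughly 8–14%. If April is counted as summer, as the Sessions schedule does, the first row becomes 9.5, 8.4 and 7.5% and the second 13.6, 12.7 and 12.0%.

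**5. Unconditional on the gate.** Power for heat-related illness at 70 households per cluster, from the protocol's own inputs, is about 0.83. Treating the outcomes as independent, 9.8% becomes 0.83 × 9.8 ≈ 8.1%, and 8.1–13.7% becomes about 6.7–11.4%.

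**6. If neither outcome is affected.** The gate opens by chance with probability 0.05, so family-wise error cannot exceed 0.05 however many quality-of-life contrasts follow.

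**The case against.** The strongest reply is that the protocol claims error control across the two outcomes, and the sequence supplies it. The word introducing the seasonal analyses marks them as additional, results are promised as estimates with CIs, and no success rule is attached to them. The Sample size and Statistical analysis sections both point to one repeated-measures model. Labels such as supportive are commonly left to an SAP.

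Much of this stands. A reader might infer that each contrast is a confirmatory test at 0.05 and that any one suffices, so that error control fails. The text does not say so. A reader might also count the year-on-year comparison as three visit-specific tests. With summer and winter that makes five contrasts and, under the same assumptions, a chance of 21–22%. The wording can equally mean one pooled contrast, so that figure should not be used. Nor does inflation follow whenever the gate opens: it needs no true quality-of-life effect and freedom to choose among contrasts. The April visit in Table 3 is at most a small mismatch with Table 1, since the Sessions schedule counts April as summer, and it has no bearing on alpha.

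What the reply does not remove is the conflict between the two overall readings. Setting the seasonal analyses aside as supportive still leaves a pooled difference in one section and a year-on-year change in the section headed as the primary analysis. That is a contradiction within the protocol and not an omission an SAP would be expected to fill.

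**Conclusion.** The concern holds in a limited form. Step 2 of the sequence is not tied to one contrast, and the sections that describe it conflict. Family-wise control is therefore not secured in the case where heat-related illness truly improves and quality of life does not. It is not shown to fail, and under the global null it stays within 5%.

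With the gate open, the false-positive chance is about 9.8% if either overall reading could count, and roughly 8–14% for one overall contrast plus the two seasonal ones. These figures rest on contrasts tested at 0.05, any of which could count, and on an exchangeable correlation; the 8–14% range also rests on assumed correlations of 0.3–0.7. Apart from error rates, the year-on-year contrast is not the quantity the sample size supports and would be near zero under an equal benefit in both years.

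**What to change.** In the Primary outcome analysis section, state that step 2 of the fixed sequence is one contrast: the between-arm adjusted mean difference from the single repeated-measures mixed model over the scheduled visits, as the Sample size and Statistical analysis sections already indicate. Name the visit treated as baseline, if there is one. State that the year-on-year, visit-specific, summer-only and winter-only results are supportive estimates with 95% CIs. If the sponsor wants a confirmatory claim from one of them, place it later in the sequence, tested only if the step 2 contrast is significant.

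This costs a few sentences before the data are seen. It needs no new data or households, and quality of life keeps its full 0.05. Splitting alpha equally over three contrasts (0.0167 each) would instead cut power for a 4-point difference at 60 households from about 0.84 to 0.71 by normal approximation. The downside is that a season-specific or year-on-year result alone could no longer establish the co-primary outcome.
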